## Table 4. Study design and flow chart………………………………………………………21

Table 5 Study plan…………………………………………………………………..........22

Table 6 Lapatinib starting dose and dose reduction schedule…………………………….32

Table 7 Dose reduction criteria and guideline for management of lapatinib associated toxicity…………………………………………………………………………...32

Protocol synopsis

**A pilot feasibility study to evaluate the efficacy of lapatinib in eliminating cytokeratin-positive tumour cells circulating in the blood of women with breast cancer**

Principal Investigator [name]

Dep of Medical Oncology

University Hospital of Heraklion

Study Chairman: [name]

Professor of Medical Oncology

Dep of Medical Oncology

University Hospital of Heraklion

Study centre(s) and number of subjects planned

This study will be conducted in the Department of Medical Oncology at the University General Hospital of Heraklion, in Greece. Twenty women with metastatic breast cancer are planned to participate in this study.

Objectives

To evaluate the efficacy of lapatinib in eradicating chemo- resistant tumour cells circulating in the blood of patients with breast cancer. These cells will be detected using immunofluorescence microscopy on Peripheral Blood Mononuclear Cell (PBMC) cytospins.

Study design

Open label, single-arm exploratory phase II clinical trial

Target subject population

Patients with metastatic breast cancer who have persistent detection of tumour cells in the peripheral blood (defined as ≥1 CTC per 106 PBMCs detected by immunofluorescence microscopy) despite at least one line of chemotherapy will receive lapatinib for a minimum of one month unless disease progression (defined by RECIST) occurs at an earlier time point. Prior hormonal therapy administered for metastatic disease is allowed.

Investigational product, dosage and mode of administration

Lapatinib 1500 mg/day orally

Duration of treatment

All patients will receive lapatinib for a minimum of one month unless clinical disease progression (defined by RECIST criteria) occurs at an earlier time point. At the end of the 1-month period patients will be assessed for the presence of CTCs in peripheral blood. Those with decreased or stable CTC counts will continue treatment and will be assessed every month. Patients with increased CTC counts will be withdrawn from the study if further increase is documented at re-assessment after the second treatment course. In subsequent cycles, treatment will be also discontinued in case of two consecutive increases in CTC values. Moreover, treatment will be discontinued in case of disease progression, occurrence of unacceptable toxicity or consent withdrawal, irrespectively of CTC counts.

Outcome variables

**Efficacy**

- **Primary outcome variable**:
- Effect of lapatinib on HER2-positive CTC counts.
- **Secondary outcome variables:**
- Correlation of the kinetics of CTCs with response to treatment
- Safety of lapatinib treatment in this patient population

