CTCs have been also identified in 40-60% of patients with metastatic breast cancer (15-16). Using a newly developed CellSearch system (Veridex) that was designed to detect tumor cells in peripheral blood, Cristofanilli et al (16) showed that the level of CTCs before a new treatment is initiated as well as the level measured three to four weeks after treatment initiation, are useful predictors of progression-free and overall survival. Specifically, patients with levels of CTCs equal to or higher than 5 per 7.5 ml of whole blood as compared with the group with fewer than 5 CTCs per 7.5 ml, had a worse prognosis. Moreover, the outcome of patients with ≥5 CTCs at baseline but <5 at the first follow-up visit was comparable to that of patients with <5 CTCs both at the the first follow-visit and at baseline.

The above findings imply the significance of CTCs as a prognostic tool in cancer treatment. However, since the presence of CTCs is the necessary (although not sufficient step) in the metastatic process, these cells represent the subset of tumor cells that lead to the development of metastasis. Metastatic cells can have a very different molecular profile from the tumor of origin, therefore CTCs might theoretically be used for the identification of the molecular signature of the specific tumor over time. Thus, chemotherapeutic drugs and molecularly targeting agents might be more efficiently tested in CTCs rather than the primary tumor.

##

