The principal mechanism by which HER2 transmits signals is the formation of heterodimeric receptor complexes with EGFR, HER-3 or HER-4. It has been suggested that HER-2, being the most common heterodimerization partner of EGFR, may play an important role in the oncogenic activity of EGFR. In turn, EGF stimulation of EGFR, leads to activation of HER2 by heterodimerization (38). Thus, combined inhibition of both EGFR and HER2 may be more efficacious than targeting either one of them alone. Lapatinib is a selective reversible inhibitor of both EGFR and HER2 tyrosine kinases that inhibits receptor phosphorylation and downstream PI3K/Akt and MAP kinase signalling pathway in cells overexpressing EGFR or HER-2 (24, 25). Lapatinib has been shown to exert both antiproliferative and pro-apoptotic effects against breast cancer and represents an ideal candidate to be used for the elimination of circulating breast cancer cells. The feasibility of this approach has been demonstrated by the administration of trastuzumab in patients with breast cancer that resulted in the elimination of circulating cells in 22 out of 30 patients (33).

A significant amount of data point to the presence of CTCs in the peripheral blood of patients with solid malignancies as a prognostic indicator of poor clinical outcome (39). However, besides the clear prognostic value of CTCs, it is not yet known whether additional treatment targeting CTCs that persist despite systemic treatment, will translate into a benefit in progression-free and/or overall patient survival. At least theoretically, patients could benefit from a secondary treatment aiming in eliminating micrometastatic disease. This treatment could be tailored on the basis of the molecular profile of CTCs which reflect the subset of tumor cells that is potentially capable of giving rise to overt metastatic disease. This approach could be applicable either in the adjuvant and/or the metastatic disease setting.

Lapatinib is considered a novel and promising agent in the treatment of human breast cancer. Based on the above data, it could be very important and clinically relevant to know if lapatinib is capable of eliminating occult tumour cells circulating in the blood of breast cancer patients.

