# 2. Study objectives

In the present study we would like to evaluate the efficacy of lapatinib in eliminating chemo- and/or hormone- resistant tumour cells circulating in the blood of patients with breast cancer.

- 1. **Primary objective**

The efficacy of lapatinib on HER2-positive CTCs will be measured by quantitative analysis of circulating tumour cells in the blood before, during and after the completion of lapatinib treatment. These cells will be detected by immunofluorescence microscopy on cytospins prepared from peripheral blood mononuclear cells (PBMCs) isolated by ficoll-hypaque density gradient centrifugation.

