2.3. Exploratory Objectives

- Detection of cytokeratin-positive cells by immunofluorescence microscopy
- Detection of cytokeratin-positive/EGFR- positive CTCs (immunofluorescence microscopy)

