## 3.1 Overall study design and flow chart

Patients will receive lapatinib monotherapy 1500 mg/day for a period of at least one month depending on their response and the clinical status of their disease.

- In this pilot study 20 women with metastatic breast cancer who have circulating occult tumour cells in the blood (defined as the presence of ≥ 1 CTC/ 106 PBMCs detected by immunofluorescence microscopy) despite previous chemotherapy and hormone therapy will be treated with lapatinib. All patients will be enrolled in the Medical Oncology Unit at the University Hospital of Heraklion
- All patients will receive lapatinib for a minimum of one month unless clinical disease progression (defined by RECIST criteria) occurs at an earlier time point. At the end of each month period patients will be assessed for the presence of CTCs and treatment will be administered accordingly as described above.
- Open label trial
- Non randomised
- Primary outcome variable: effect of lapatinib on tumor cells circulating in the blood of breast cancer patients
- Target patient population: Patients with metastatic breast cancer who have been previously treated with chemotherapy and/ or hormonal therapy
- Treatment with lapatinib monotherapy 1500 mg/day

Study flow chart is presented in Table 4.

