## Table 4. Study design and flow chart

| **SCREENING PERIOD DAY -21 to 0**  Patient informed consent; past medical history; demography; tumour assessment (chest X‑ray, computerised tomography [CT] scan and bone scan), CTCs assessment (double staining immunofluorescence microscopy for HER2/cytokeratin) |
| --- |
|  |
| **MAIN TREATMENT PERIOD (1 MONTH)**  Patients evaluated for concurrent illness/therapy; physical examination, adverse events at all visits (every month)  Every month: haematology; biochemistry; tumour assessment, CTCs assessment (double staining immunofluorescence experiments)  At 3 months (or at any time in case of suspected clinical disease progression): chest X‑ray, computerised tomography [CT] scan and bone scan) |
|  |
| **SECOND TREATMENT PERIOD**  Patients evaluated for concurrent illness/therapy; physical examination, adverse events at all visits (every month)  Every month: haematology; biochemistry; tumour assessment, CTCs assessment (double staining immunofluorescence experiments)  Every 3 months (or at any time in case of suspected clinical disease progression): chest X‑ray, computerised tomography [CT] scan and bone scan)  . |

Table 5 STUDY PLAN

| Study plan | Screening | Start of treatment | Treatment | | | | | | Discontinuation |
| --- | --- | --- | --- | --- | --- | --- | --- | --- | --- |
| Day (or week) | -21 to  -7 | **0** | +4we | +8we | +12we | +16 we | +20 we | +24 we |  |
| Visit | V1 | V2 | V3 | V4 | V5 | V6 | V7 | V8 |  |
| Informed consent | X |  |  |  |  |  |  |  |  |
| Medical history | X |  |  |  |  |  |  |  |  |
| Pregnancy test (if appropriate) |  | Xa |  |  |  |  |  |  |  |
| Inclusion/exclusion criteria | X | X |  |  |  |  |  |  |  |
| Physical examination including Vital signsb / Performance Status / weight |  | X | X | X | X | X | X | X | X |
| Concurrent medication |  | Xc | X | X | X | X | X | X | X |
| ECG |  | X |  |  |  |  |  |  |  |
| Clinical chemistry/ Hematologyb |  | X | X | X | X | X | X | X |  |
| Tumour assessment | X |  |  |  | X |  |  | X |  |
| CTCs assessment (CTCs number, double staining immunofluorescence microscopy | X | X | X | X | X | X | X | X | X |
| Adverse eventsc |  |  | X | X | X | X | X | X | X,de |
| Dispense study medication |  | X | X |  |  | X |  |  |  |
| Survival |  |  |  |  |  |  |  |  | Xf |

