## 3.3 Selection of study population

### 3.3.1 Inclusion criteria

For inclusion in the study subject must fulfil all of the following criteria:

1. .Provision of written informed consent
2. Histologically or cytologically‑confirmed breast cancer
3. Metastatic breast cancer (stage IIIB and IV). EGFR and/or HER-2 expression on the primary tumor is not mandatory.
4. Patients should have received at least one course of standard systemic chemotherapy for their metastatic disease. Prior hormonal therapy is allowed.
5. Patients should have achieved objective response (CR or PR) or stable disease to previous treatment.
6. There should be at least one month between the end of chemotherapy treatment and trial entry. In case of prior Herceptin administration, 3 months are required to have elapsed before study entry.
7. Detection of at least 1 CTC/106 PBMCs despite the previous administration of chemotherapy and/or hormonal therapy.
8. HER-2 expression on CTCs.
9. Age 18 years and over Adequate organ function

Haematological function:

- Absolute neutrophil count (ANC) ≥1.5 x 109/L
- Platelet count ≥100 x 109/L and
- Haemoglobin ≥9 g/dL (may be transfused to maintain or exceed this level)

Liver Function:

- Total bilirubin <1.5 x upper limit of normal (ULN)
- AST, ALT <2.5 x ULN in patients without liver metastases; <5 x ULN in patients with liver metastases

Renal function:

- Serum creatinine ≤1.25 x ULN or calculated creatinine clearance ≥50 mL/min

1. LVEF within institutional normal range
2. Eastern Cooperative Oncology Group (ECOG) performance status (PS) of 0 to 2
3. Life expectancy of at least 12 weeks

###

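### The primary outcome is the HER2-positive CTC count, but the stated question is elimination of circulating tumour cells; a fall in the first does not by itself answer the second

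*Protocol*

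**What the plan says.** The protocol states its primary outcome in three places:

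- Synopsis, Outcome variables: "Effect of lapatinib on HER2-positive CTC counts".
- Section 2.1: "The efficacy of lapatinib on HER2-positive CTCs will be measured by quantitative analysis of circulating tumour cells in the blood". The target is HER2-positive cells, but the measurement is worded for circulating tumour cells in general.
- Section 3.1: "Primary outcome variable: effect of lapatinib on tumor cells circulating in the blood of breast cancer patients", with no HER2 restriction.

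The study title aims at cytokeratin-positive tumour cells, whatever their HER2 status. The synopsis objective and the opening of section 2 speak of eradicating or eliminating treatment-resistant circulating tumour cells, again without HER2. Section 1.4 calls it "clinically relevant to know if lapatinib is capable of eliminating occult tumour cells circulating in the blood of breast cancer patients".

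The count that matches the title appears in section 2.3 as an exploratory item: "Detection of cytokeratin-positive cells by immunofluorescence microscopy".

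Entry requires "HER-2 expression on CTCs" (section 3.3.1), with no threshold or share given, and at least 1 CTC per 10^6 PBMCs. The screening assay in Table 4 is "double staining immunofluorescence microscopy for HER2/cytokeratin". Table 5 schedules a CTC number with double staining at every visit.

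**The concern.** Patients are selected for HER2 on their CTCs, are given an inhibitor of HER2 and EGFR, and are then measured by the number of CTCs that still show HER2. A fall in that number has three possible explanations:

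1. The cells are gone.
2. The cells are still there but no longer stain for HER2.
3. HER2-positive cells have been replaced by HER2-negative ones.

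Only the first is elimination of tumour cells. The third is a real fall in HER2-positive cells, and the second is misclassification, but under both the tumour cells still circulate.

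The protocol's own background allows for a profile that changes. Section 1.2 says that "CTCs might theoretically be used for the identification of the molecular signature of the specific tumor over time". With one arm and 20 patients, no comparator would show which explanation applies. The trial could report a fall in its primary outcome while the number of circulating tumour cells was unchanged.

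**Working it through.** **Inputs.** From the protocol: 20 patients and a minimum of 1 CTC per 10^6 PBMCs at entry. It states no alpha, power, effect size or definition of clearance, so there is no planned figure to reproduce. It also gives no rate at which CTCs change HER2 status, so every share and probability below is assumed. In both illustrations the total cytokeratin-positive count is held constant, so no cell is eliminated.

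**Illustration 1: shift in the HER2-positive share.** With mean total T per sample and HER2-positive share s, the mean HER2-positive count is T × s. The relative change is s_after / s_before − 1.

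- Share 80% to 40%: 0.4/0.8 − 1 = −50%.
- Share 60% to 10%: 0.1/0.6 − 1 = −83%.

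With Poisson counts, P(zero HER2-positive) = exp(−T × s) and P(zero total) = exp(−T). Low counts give zeros by chance alone, so the proper comparator is the same probability with the share unchanged at 60%.

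| Mean total T | Share falls to 10% | Share stays at 60% | Zero total count |
|---|---|---|---|
| 2 | exp(−0.2) = 82% | exp(−1.2) = 30% | exp(−2) = 14% |
| 5 | exp(−0.5) = 61% | exp(−3) = 5% | exp(−5) = 0.7% |
| 10 | exp(−1) = 37% | exp(−6) = 0.2% | exp(−10) < 0.01% |

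The part due to the shift is the first probability minus the second: about 82 − 30 = 52, 61 − 5 = 56 and 37 − 0.2 ≈ 37 percentage points.

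**Illustration 2: loss of staining cell by cell.** Each of H baseline HER2-positive cells stops staining with probability q, with the same H in all patients and no sampling variation. The apparent reduction is q, and the expected number of 20 patients with a zero HER2-positive count is 20 × q^H.

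| H | q = 0.1 | q = 0.3 | q = 0.5 |
|---|---|---|---|
| 1 | 2.0 | 6.0 | 10.0 |
| 2 | 0.2 | 1.8 | 5.0 |
| 3 | 0.02 | 0.54 | 2.5 |
| 5 | 0.00 | 0.05 | 0.62 |

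The true reduction in tumour cells is 0% throughout, and a total cytokeratin-positive count would show 0%. The effect on zero counts is largest at the lowest counts that entry allows. With q = 0.1 and three or more cells it is negligible.

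**The case against.** Several counter-arguments have force.

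- *The target is reasonable.* Measuring a HER2-directed drug on HER2-positive cells, in patients selected for them, is a defensible choice. If HER2-negative cells take over, the HER2-positive count really has fallen, which is what the synopsis asks. This stands: the HER2-positive count should stay.
- *The restriction is not settled.* Section 3.1 has none, and section 2.1 is mixed. That is true, but the conflict itself needs resolving, and anyone following the synopsis meets the problem.
- *Overall CTC counts have other uses.* The secondary outcome on CTC kinetics and the discontinuation rule both refer to CTCs without mentioning HER2. On their wording the total may be used there. Neither place says which count is meant, and neither ties the total to the primary conclusion.
- *This is detail for the analysis plan.* The table layout is. Which count is primary, and which claim it supports, is fixed in the protocol.

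A reader might infer more: that cells losing HER2 staining are scored as eliminated, or that lapatinib is known to remove the staining. The documents support neither. They define no eliminated, responder or success category. Sections 1.3.1, 1.3.2 and 1.4 describe inhibition of kinase activity and phosphorylation, not loss of HER2 expression. Section 1.2 speaks only of a theoretical use of CTCs and of metastatic cells differing from the primary tumour.

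**Conclusion.** The concern holds as a mismatch between outcome and claim. Followed as the synopsis and section 2.1 state it, the primary result describes HER2-positive CTCs. It does not on its own answer whether circulating tumour cells were reduced or eliminated, which is the question in the title, section 1.4 and section 2. This follows from the definition of the count and needs no assumption about how often HER2 status changes.

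The size of any bias is unknown. The illustrations run from negligible to large, and the 82% and 61% zero-count figures must be read against 30% and 5% from ordinary sampling at low counts. In a pilot of 20 patients with no stated test, this is a point that should be corrected, not one that invalidates the trial.

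**What to change.** Reconcile the primary outcome in the synopsis, section 2.1 and section 3.1:

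1. Keep the HER2-positive count and analyse the total cytokeratin-positive count alongside it, as co-primary or as a key supporting outcome, from the same double-stained slides at the same visits.
2. Tabulate HER2-positive, HER2-negative and total cytokeratin-positive counts for each patient at each visit.
3. Report a change in the HER2-positive count as an effect on HER2-positive CTCs. Claim reduction or elimination of circulating tumour cells only on the total cytokeratin-positive count.
4. State which count the secondary kinetics outcome uses. The discontinuation passages are equally silent on which count they mean and must be reconciled with the rest.

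Table 4 names the HER2/cytokeratin pair at screening and only double staining afterwards. The treatment visits should name the pair too; the primary outcome already requires it.

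The cost is wording and one further tabulation, with no new sample, stain or patient. The downside is that a real effect on HER2-positive cells may not support the broader elimination claim when HER2-negative cells persist. Point 3 handles this by reporting the two results separately.

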**Exploratory**

- Detection of cytokeratin-positive cells
- Detection of cytokeratin-positive/EGFR-positive CTCs

#

# 1. Introduction

**1.1 Breast cancer**

Breast cancer is the most common cancer among women and is the second leading cause of female death (American Cancer Society, 1994). Although a small percentage of patients with metastatic breast cancer achieve long-term disease-free survival, the disease at this stage is not curable and therapy is only palliative.

## Over the last two decades, chemotherapy and endocrine therapy have become the most important therapies in the treatment of patients with early or metastatic breast cancer. Adjuvant chemotherapy and/or endocrine therapy represent the standard of care for women with early breast cancer expressing hormone receptors. In the metastatic setting endocrine treatments are the therapy of choice for asymptomatic, non-life-threatening disease in patients with oestrogen receptor and/or progesterone receptor (ER/PgR)-positive tumours; chemotherapy has to be used if metastases become symptomatic or if specific organ function is impaired. Surgery or radiotherapy is confined to specific indications and is mainly used in combination with systemic treatment.

**1.2 Disseminated tumor cells in patients with breast cancer. Clinical significance**

Breast cancer is considered a systemic disease since early tumour cell dissemination may occur even in patients with small tumours; several investigators using immunocytochemistry or real time PCR (RT-PCR) have shown that cytokeratin-positive epithelial cells could be identified in the bone marrow aspirates or the peripheral blood of otherwise metastases-free patients with stage I and II breast cancer (1,2). The clinical importance of the immunocytochemical detection of occult tumour cells in the bone marrow has been confirmed in many prospective studies to represent an independent predictive and prognostic factor for distant relapse and reduced survival (3-6).

A molecular methodology to detect occult tumour cells is based on the amplification of cytokeratin 19 by RT-PCR (CK-19) mRNA; this assay is capable of detecting one tumour cell among one million normal cells and is at least 10 times more sensitive than immunocytochemistry (7). Indeed, occult tumour cells have already been identified by nested RT-PCR in the peripheral blood of breast cancer patients by many investigators (8-11).

Our group has recently evaluated the presence and the prognostic significance of circulating tumour cells (CTCs) expressing the CK-19 mRNA by nested RT-PCR in the peripheral blood of 148 patients with stage I and II breast cancer before the initiation and after the completion of adjuvant chemotherapy (11, 12). CK-19 mRNA-positive cells could be detected in almost 30% of patients before adjuvant chemotherapy, and multivariate analysis demonstrated that the presence of these cells was an independent prognostic factor for decreased DFI (p=0.001) and overall survival (p=0.01). Moreover, adjuvant chemotherapy failed to eliminate the circulating CK-19 mRNA-positive cells in almost half of the patients while an additional 20% of patients developed CK-19 mRNA-positive cells in the blood during the treatment. The risk of relapse was 3.8 (95% C.I. 1.06-13.56) times higher and the DFI was significantly reduced (p=0.03) if CK-19 mRNA-positive cells were detectable after the completion of adjuvant chemotherapy in patients with <3 involved axillary lymph nodes. In a recently completed study our group showed that the prognostic significance of the detection of circulating CK-19 mRNA-positive cells is also applied in patients with disease stage I (13). Similarly to our findings, Braun et al (14), using an immunocytochemical technique, studied 23 patients with inflammatory and 36 with operable breast cancer who had more than 4 axillary lymph nodes involved, for the presence of occult bone marrow breast cancer cells before and after the completion of adjuvant chemotherapy; they found that only 48.3% of the patients who had CK-positive cells in the bone marrow before treatment became CK-negative post-treatment; multivariate analysis showed that the detection of CK-positive cells post-chemotherapy represents an independent poor prognostic factor for reduced overall survival.

CTCs have been also identified in 40-60% of patients with metastatic breast cancer (15-16). Using a newly developed CellSearch system (Veridex) that was designed to detect tumor cells in peripheral blood, Cristofanilli et al (16) showed that the level of CTCs before a new treatment is initiated as well as the level measured three to four weeks after treatment initiation, are useful predictors of progression-free and overall survival. Specifically, patients with levels of CTCs equal to or higher than 5 per 7.5 ml of whole blood as compared with the group with fewer than 5 CTCs per 7.5 ml, had a worse prognosis. Moreover, the outcome of patients with ≥5 CTCs at baseline but <5 at the first follow-up visit was comparable to that of patients with <5 CTCs both at the the first follow-visit and at baseline.

The above findings imply the significance of CTCs as a prognostic tool in cancer treatment. However, since the presence of CTCs is the necessary (although not sufficient step) in the metastatic process, these cells represent the subset of tumor cells that lead to the development of metastasis. Metastatic cells can have a very different molecular profile from the tumor of origin, therefore CTCs might theoretically be used for the identification of the molecular signature of the specific tumor over time. Thus, chemotherapeutic drugs and molecularly targeting agents might be more efficiently tested in CTCs rather than the primary tumor.

##

